A key partner in the implementation of our projects has been the Kinshasa School of Public Health (KSPH) with whom UNC has worked since 2000. Other partners include the Bureau *des Oeuvres Médicales Diocésaines* (Catholic Health Board) the Salvation Army, MOH agencies such as the National AIDS Control Program (PNLS), the National Tuberculosis Control Program (PNT), and PRONANUT as well as international organizations including the Elizabeth Glaser Pediatric AIDS Foundation, UNICEF, Médecins Sans Frontières, Action Against Hunger, the German Agency for Technical Cooperation (GTZ), the Clinton Foundation and the Global Fund to Fight AIDS, Tuberculosis, and Malaria.

In collaboration with the KSPH, we have established technical, administrative/logistical and financial support systems based at a central office in Kinshasa. Our proposed management and implementation plan builds on this collaboration, and takes advantage of the extensive experience and structures already in place.

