Since 2002 and under the leadership of [name], the University of North Carolina at Chapel Hill (UNC) has collaborated with the Congolese Ministry of Health (MoH) and national and local organizations to improve Human Immunodeficiency Virus (HIV) prevention and care through the University Technical Assistance Program (UTAP) with support from various donors. Currently, 44 maternities are supported by our UNC-DRC team serving more than 50,000 pregnant women yearly. These maternities are generally part of a health facility that also hosts a well-child clinic where infants are typically monitored on a monthly basis. As stated above, routine immunization takes place during these monthly visits. To minimize the implementation cost, six of the 44 health facilities with the largest number of deliveries per year will be selected to be part of the study – 3 in urban and 3 in peri-urban areas. Prior to selection, direct observation will be carried out in eligible health facilities to collect information on key characteristics (workload per staff, type of management [government vs private], general infrastructure) that are likely to affect the quality of care. Facilities will be matched for these characteristics prior to randomization. This approach will ensure for example, that health care facilities at the periphery of the city that might have lower patient volumes than facilities in urban areas and serve populations more likely to be socio-economically disadvantaged are included. The selected six facilities will be randomized into 3 groups to receive the following interventions: 1) continuation of current care practices (usual care), 2) implementation of BFHI steps 1-9 in maternities (BFHI steps 1-9), and 3) implementation of BFHI steps 1-9 in maternities and provision of breastfeeding support including culturally appropriate educational messages and metaphors as the ongoing aspect of step 10 in well-child clinic (BFHI steps 1-9 +well-child clinic). The study will be implemented in 2 phases.

Pre-intervention phase

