Data from the questionnaires will be double entered into an Access database, compared for consistency and cleaned as needed. The proportion of infants initiating breastfeeding within 1 hour of birth and who are exclusively breastfed at 14 weeks and 6 months post-partum are the primary outcomes that will be measured and compared between intervention and control groups. To estimate the effect of implementing the *Ten Steps* in maternities on the rate of breastfeeding initiation within 1 hour of birth and that of exclusive breastfeeding at 6 months, the usual care group will provide the counterfactual, and the proportion of infants with each of the primary outcomes in the BFHI steps 1-9 group will be compared to the proportion of infants with the same outcomes in the usual care group. To determine the effect of providing breastfeeding support in well-child clinics in addition to implementing the Steps 1-9 in maternities on the rate of EBF at 6 months, the BFHI steps 1-9 group will serve as control and the proportion of infants with the outcome in the intervention group ( BFHI steps 1-9+well-child clinic) will be compared to that of infants with the outcome in the BFHI steps 1-9 arm.

All analyses will be conducted by intent-to-treat (38), meaning that mother-infant couples will be classified to have received the intervention that their facility was randomized to whether they continued to come to the facility or not after initial discharge from the maternity and the level of uptake of the *Ten Steps* in the facility. Baseline characteristics of mother-infant pairs will be compared between interventions and control groups to check for any imbalance that may persist despite randomization. Pearson chi-square will be used to compare categorical variables and T-test will be used for continuous variables assuming they are normally distributed. Normality will be formally evaluated using Kolmogorov–Smirnov test. For non-normally distributed continuous variables, Wilcoxon Rank-sum test will be used. Generalized Estimation Equation (GEE) and Log Binomial model will be used to estimate the prevalence ratio comparing interventions groups to controls. In GEE, the dependence within cluster is treated as nuisance, and valid inference (or confidence interval) is produced for population average effects as long as the mean structure is correctly specified, even if the dependence structure is misspecified (39).

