The sample size of 150 mother-infant pairs per maternity is based on a series of power calculations using various prevalence estimates of the prevalence of EBF at 6 months in the control group (15% to 35% for usual care) and a minimum expected effect size of RR = 1.5 for the first objective – comparison of BFHI steps 1-9 to usual care (figure 2.a) and a prevalence of EBF at 6 months in the BFHI steps 1-9 group of 45 to 65% and a minimum expected effect size of RR = 1.3 for the second objective – comparison of the provision of support in the well-child clinics in addition to the implementation of BFHI steps 1-9 in maternities vs. BFHI steps 1-9 in maternities alone (figure 2.b). Assuming two-tailed Person chi-square test with α values of .05, the sample size of 900 mother-infant pairs should provide adequate power to detect a modest difference in the proportion of infants exclusively breastfed at 6 months between BFHI alone and usual care arms or between BFHI steps 1-9 + well-child clinics arm and BFHI steps 1-9 alone.

To determine the number of clusters of size n = 150 that will be needed to achieve an 80% power, we used the formula proposed by Hayes and Bennett (40). Assuming a coefficient of variation of 25% (which is generally considered reasonable), and a 20% prevalence of exclusive breastfeeding in the “usual care” group, we varied various expected prevalence of EBV that could be achieve with the implementation of the Ten Steps. Results are presented in the figure 3 below. Once the prevalence of EBF in the intervention group reaches 40%, the number of clusters needed falls below 4.

**Figure 2.** Power estimate curves for: a- detecting a minimum effect size of RR = 1.5 comparing the prevalence of EBF at 6 months in the BFHI steps 1-9 group to that in the usual care group and b- detecting a minimum effect size of 1.3 comparing prevalence of EBF at 6 months in BFHI steps 1-9 + well-child clinic group to that in BFHI steps 1-9 group for a sample of n = 150 per health facility, n = 300 per randomization group, and n = 900 total for various prevalences of exclusive breastfeeding at 6 months.

Figure 3. Number of clusters of size 150 needed to achieve 80% power for a fixed coefficient of variation of 0.25 by the expected proportion of EBF in the intervention group, assuming a 20% prevalence of EBF in the usual care group.

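### Facilities are matched before randomisation, but neither the analysis nor the sizing reflects it, and the stated robust GEE inference is not valid with two facilities per arm

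*Protocol*

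**What the plan says.** All references are to the Protocol, section B, Proposal Narrative.

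- **Project Design and Implementation Plan.** Six facilities are chosen, "3 in urban and 3 in peri-urban areas". They are characterised by workload per staff, type of management and infrastructure, and then: "Facilities will be matched for these characteristics prior to randomization". Next, "The selected six facilities will be randomized into 3 groups". The number and size of the matched sets are not given, nor is it said that allocation takes place within sets.
- **Evaluation, analysis.** "Generalized Estimation Equation (GEE) and Log Binomial model will be used to estimate the prevalence ratio comparing interventions groups to controls". Each objective is a contrast of two arms. On correlation, the text says "In GEE, the dependence within cluster is treated as nuisance" and treats a correctly specified mean as sufficient for valid intervals. No matching factor and no allowance for the number of clusters appears.
- **Evaluation, sample size.** Power is computed under this premise: "Assuming two-tailed Person chi-square test with α values of .05". For the cluster count, "we used the formula proposed by Hayes and Bennett", with coefficient of variation 0.25 and 20% exclusive breastfeeding (EBF) under usual care. The number needed is said to drop below 4 once the intervention arm reaches 40%.

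**The concern.** Matching before randomisation is a design feature, and the analysis should either use it or say why it does not. Here the design section introduces it and the evaluation section does not take it up, in the model or in the sizing.

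The larger problem lies in the inference that is stated. Robust GEE standard errors are justified by a large number of clusters. The contrast for each objective rests on four facilities, two per arm. The claim that a correct mean model is enough for valid intervals does not hold at that number. At stake is whether a significant result on early initiation or EBF can be believed.

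**Working it through.** **Inputs from the Protocol:** 6 facilities and 3 arms, hence 2 per arm if equal; 150 pairs per facility, 135 after 10% loss; coefficient of variation k = 0.25; 20% vs 40% EBF; two-sided α = 0.05; 80% power.

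**Assumed, because not given:** two matched sets of three with one facility per arm in each; the within-set correlation ρ of facility effects, varied from 0 to 0.9; third arm at 52%.

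**1. The Protocol's own cluster count.** Hayes-Bennett per arm:

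c = a + (1.96 + 0.84)² × [p0(1−p0)/m + p1(1−p1)/m + k²(p0² + p1²)] / (p0 − p1)², with a = 1 unmatched and a = 2 matched.

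At m = 150, the bracket is 0.00107 + 0.00160 + 0.0625 × 0.20 = 0.01517. Dividing by 0.04 and multiplying by 7.849 gives 2.98.

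- Unmatched: 3.98, which agrees with the stated result.
- Matched, same k: 4.98, which does not.

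So the sizing is unmatched.

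**2. Size of the robust test, no set effect.** With arm indicators only, the sandwich variance of an arm mean from two facilities is the sum of squared residuals over 2², half the usual s²/2. The z statistic is then √2 times a t statistic on 2 df:

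P(|t₂| > 1.96/√2 = 1.386) = 1 − 1.386/√(2 + 1.386²) = 1 − 1.386/1.980 = 0.30.

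Only the residuals of the two compared arms enter, so fitting all three arms in one GEE does not help.

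**3. What the sets do to the standard error.** At 20% in both arms, with 2 facilities per arm and m = 135, the true variance of the difference is

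0.16/135 + 0.25² × 0.20² × (1 − ρ) = 0.001185 + 0.0025(1 − ρ).

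The SD is 0.061, 0.049 and 0.038 at ρ = 0, 0.5 and 0.9. An unmatched standard error averages about 0.06 throughout, so before the few-cluster problem it is about 0%, 22% and 60% too large. The two errors oppose each other. Simulated type I error of the robust z test falls from 30% (ρ = 0) to 24% (0.5) and 18% (0.9), and is never near 5%.

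**4. Facility-level alternatives.** 100,000 simulated trials per scenario: lognormal facility effects, binomial counts, analysis of log prevalence, 20% vs 40%.

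| Analysis | Type I error, ρ = 0.5 | Power at ρ = 0 | 0.25 | 0.5 | 0.75 | 0.9 |
|---|---|---|---|---|---|---|
| Two arms, unmatched t, 2 df | 3.5% | 28% | 29% | 29% | 31% | 33% |
| Three arms pooled, unmatched, 3 df | 3.1% | 41% | 41% | 43% | 47% | 50% |
| Three arms pooled, set term, 2 df | 4.8% | 30% | 35% | 42% | 54% | 66% |

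The set-term model stays near 5% at every ρ tried. A two-arm paired test (1 df) has 19% power at ρ = 0.5. Median interval widths on the log scale at ρ = 0.5 are 2.02, 1.53 and 1.58 in the order of the table.

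**5. Adding the set to a sandwich GEE.** In the two-arm case the sandwich standard error is half the paired one, so the test rejects when |t₁| > 0.98. Under normality that is 1 − (2/π) arctan(0.98) = 0.51. With binomial counts, where ties occur, simulation gives about 54%.

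**The case against.** **The set structure is inferred.** The Protocol does not say there are two triplets or that allocation is within them. The matching may have been meant for selection and balance. This stands. It is why the fix begins with stating the sets, and why the set term is conditional on the answer.

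**Silence on covariates is not exclusion, and a SAP may settle it.** This stands as far as the set term goes: nothing says that matching will be left out of the model. It does not cover the inference. The Protocol itself names the model and gives a justification that fails with this few clusters.

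**The plan throws away the precision bought by matching.** A reader might infer this from the move from 29% to 42% power at ρ = 0.5, with an interval 22% narrower (1.58 vs 2.02). The figures do not support it. That comparison changes two things at once. Pooling over three arms without a set term already gives 43% and a width of 1.53, so at ρ = 0.5 the gain comes from pooling. Nor are the plan's own intervals too wide: as stated they are too narrow. Excess width would arise only after a correction for few clusters.

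**Breaking the matching is defensible with so few facilities.** This stands in part. The unmatched pooled model has more power when matching is weak, at the price of being conservative when matching works.

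**Conclusion.** The concern holds in this form: the matching appears in the design but in neither the stated analysis nor the sizing, and robust GEE inference with two facilities per arm is not valid. Its type I error is about 18 to 30%, on the Protocol's coefficient of variation of 0.25, 135 pairs per facility, equal allocation, normal quantiles and no small-sample correction.

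Whether precision is lost by ignoring the sets cannot be decided from the Protocol, because the within-set correlation is not given and allocation within sets is not stated. The power figures depend on both assumptions and on a third arm at 52%.

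No analysis rescues power here. For objective 1 even the better facility-level models give about 42% at ρ = 0.5. For objective 2 (40% vs 52%) the set-term model has 8.6% against 9.5% for the unmatched two-arm t-test at ρ = 0, and 10.7% against 8.2% at 0.5. The case for change is valid inference first, with a modest and conditional gain in power.

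**What to change.** 1. **Project Design and Implementation Plan:** state the matched sets and whether allocation is within them, for example two sets of three with one facility per arm in each.
2. **Evaluation, analysis:** make the primary analysis one facility-level model of log prevalence on all six facilities, with residual variance pooled over the three arms and t quantiles. If allocation is within sets, include a set term (2 df). If it is not, omit it (3 df). Take both contrasts from this model, and do not use a two-arm paired test.
3. **State the trade-off.** The set term costs one degree of freedom. Against the unmatched pooled model, power is 30% vs 41% at correlation 0, 42% vs 43% at 0.5, and 66% vs 50% at 0.9. The unmatched pooled model is conservative when matching works (3.1% type I error at 0.5).
4. **If GEE is kept as a secondary analysis,** use a small-sample method, and do not add the matched set without one.
5. **Evaluation, sample size:** say that the cluster count is the unmatched form, or redo it to fit the chosen analysis.

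The cost is wording only, with no new data or participants. The pooled model assumes equal between-facility variance on the log scale across arms, which a single coefficient of variation already implies.

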Following randomization of health facilities to one of the three interventions - BFHI steps 1-9, BFHI steps 1-9 plus well baby, usual care - each hospital in the BFHI steps 1-9 and BFHI steps 1-9 plus well baby groups will be assessed as to readiness for implementing the *Ten Steps* and the hospital leadership – medical and administrative - will be provided with evidence on the importance of the *Ten Steps*. Health professionals (including doctors and nurses) and support staff of maternities randomized to BFHI steps 1-9 and maternities and well-child clinics randomized to - BFHI steps 1-9+well child clinic arms will be provided with 20 hours of training with the UNICEF/WHO course (34). In addition, staff of maternities from facilities randomized to BFHI steps 1-9 and those from maternities and well-child clinics randomized to BFHI steps 1-9+well child clinic arms will receive two additional hours of training on how to listen, to learn from mothers, to establish good relationships, to build mothers' confidence, and to offer support, taken from the WHO/UNICEF Breastfeeding Counseling Course (35). The training will be done in groups with actual mothers and babies in well-child clinics followed by a 30-minute debriefing in groups for the staff to share their experiences and give feedback. Copies of the UNICEF norms and existing guidelines for the encouragement of breastfeeding (36) will be offered to all health facility managers randomized to BFHI steps 1-9 and BFHI steps 1-9+well child clinic arms and support will be provided, as needed, for the implementation of each of the *Ten Steps*. In DRC, following discharge from maternity, mother and infant are expected to return to the delivery facility for birth certificate and a general check-up of both the mother and her infant. But this visit is often neglected by maternities and attendance is generally low. In maternities randomized to interventions, an effort will be made to make sure that mother and baby effectively return for this visit including home visit for those who fail to return in the first 3 weeks. To maintain a continuous contact and ensure that mothers who need support can access it during the period between the first week visit in the maternity and the first well-child clinic visit at 6 weeks, the phone number of the maternity nurse will be given to each mother and she will be encouraged to call or return to the maternity if she experience any difficulty breastfeeding or has any question during this period. An effort will be made to assist clinic staff in handling telephone calls through the development of a job aid for handling common problems, modified from the UNC clinical job aids.

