The goals of this project are to evaluate a) the effect of this short-cut approach to implementation of BFHI steps 1-9 in maternities in Kinshasa on the rates of early initiation of breastfeeding and that of EBF at 6 months, compared to the usual care arm and b) the effect of breastfeeding support provided in well-child clinics in addition to the short-cut implementation (without accreditation) of BFHI steps 1-9 in maternities on the rate of EBF 6 months post-partum, compared to the BFHI steps 1-9 arm. WHO definitions will be used (37):[7](http://www.sciencedirect.com.libproxy.lib.unc.edu/science?_ob=ArticleURL&_udi=B6T1B-4H5GDN3-W&_user=130907&_coverDate=09%2F30%2F2005&_rdoc=1&_fmt=high&_orig=search&_origin=search&_sort=d&_docanchor=&view=c&_acct=C000004198&_version=1&_urlVersion=0&_userid=130907&md5=7b6d09c61c88f94f9356fb50cc5be97d&searchtype=a#bbib7) WHO, *Indicators for assessing breastfeeding practices*, WHO, Geneva (1992). infants will be classified as exclusively breastfed if they received only breast milk (no water, other liquids, or solids) and as early initiation of breastfeeding if breastfeeding is initiated within one hour after birth. Secondary outcomes including any breastfeeding and predominant breastfeeding will also be considered. Information on breastfeeding practices will be collected via questionnaires administered to mothers at maternity discharge, first weeks visit, and at every well-child visit up to 6 months post-partum. Although masking of the interventions will not be possible, independent interviewers will be appropriately trained and questionnaires designed in a way to help minimize reporting bias (using scripts for example to de-stigmatize undesirable answers).

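### Early initiation is compared using only two of the four maternities that deliver BFHI steps 1-9, a valid but inefficient contrast for a primary outcome settled at birth

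*Protocol*

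**What the plan says.** The Project Design and Implementation Plan states that "The selected six facilities will be randomized into 3 groups to receive the following interventions": usual care, BFHI steps 1-9 in maternities, and, as the third arm, "implementation of BFHI steps 1-9 in maternities and provision of breastfeeding support" in the well-child clinic. The legend to Figure 2 gives "n = 150 per health facility, n = 300 per randomization group, and n = 900 total", so there are two facilities per arm. The same section says that three facilities will be urban and three peri-urban, and that facilities are matched on key characteristics before randomization.

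Under Intervention Phase, maternity staff in both intervention arms receive the same course. Staff of the BFHI-alone maternities are listed together with those of "maternities and well-child clinics randomized to - BFHI steps 1-9+well child clinic arms will be provided with 20 hours of training", and both then get the same two additional hours on counselling. The first well-child clinic visit is placed at 6 weeks.

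The Evaluation section names the primary outcomes: "The proportion of infants initiating breastfeeding within 1 hour of birth and who are exclusively breastfed at 14 weeks and 6 months". Goal (a) is the effect of the maternity intervention "on the rates of early initiation of breastfeeding and that of EBF at 6 months, compared to the usual care arm". The comparison for that goal is then fixed: "the proportion of infants with each of the primary outcomes in the BFHI steps 1-9 group will be compared" with usual care. The BFHI + well-child arm enters only the second comparison, for exclusive breastfeeding (EBF) at 6 months against BFHI alone.

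**The concern.** Initiation within 1 hour is settled before discharge. At that moment the two intervention arms have, by design, been given the same thing, and the component that separates them starts weeks later and cannot act backwards. Four maternities therefore carry information on the initiation effect in objective 1, but the stated comparison uses two of them.

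In a trial of hundreds of clusters this would hardly matter. With six, the number of facilities governs both the standard error and the degrees of freedom (df) for estimating between-facility variation. The 300 mother-infant pairs in the BFHI + well-child facilities will have initiation recorded anyway, since interviews take place at maternity discharge in every arm.

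**Working it through.** **The plan's own figure.** No sample size or power is stated for early initiation. The only cluster-based figure is for EBF: fewer than 4 clusters of 150 once EBF reaches 40% against 20%, with coefficient of variation (CV) 0.25 and 80% power. The Hayes-Bennett formula per arm is

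c = 1 + (1.960 + 0.842)² × [p0(1−p0)/n + p1(1−p1)/n + k²(p0² + p1²)] / (p1−p0)².

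With p0 = 0.20, p1 = 0.40, n = 150 and k = 0.25, c = 3.98. The figure reproduces, and the same variance model is used below.

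**Inputs for early initiation.**
- Two facilities per arm, 150 pairs each (Figure 2 legend).
- Background initiation 48%: a national survey figure in Background and Rationale, not specific to Kinshasa.
- 72% under BFHI (ratio 1.5): an assumption; the protocol gives no target for initiation.
- CV: none is given for initiation. The range 0.05 to 0.25 is assumed; 0.25 is the protocol's value for EBF.
- Two-sided 5% level, as in the sample size text.

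**Standard error, equal facility variance.** The variance of the difference is proportional to 1/2 + 1/2 = 1 for two against two, and to 1/4 + 1/2 = 0.75 for four against two. The ratio of standard errors is √0.75 = 0.866, a fall of about 13%.

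**Confidence interval, unmatched facility-level analysis.** Two-sided 5% t values are 4.303 (2 df), 3.182 (3 df) and 2.776 (4 df).
- Against a two-arm analysis (4 − 2 = 2 df): 0.866 × 2.776 / 4.303 = 0.559, 44% narrower.
- Against a three-arm model that borrows variance from the third arm (6 − 3 = 3 df): 0.866 × 2.776 / 3.182 = 0.756, 24% narrower.

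**If allocation is within two matched sets of three**, one further df goes to the set effect. The pooled contrast has 6 − 1 − 1 − 1 = 3 df, a three-arm model has 2, and the two-arm contrast has 1. Against the three-arm model the half-width ratio is 0.866 × 3.182 / 4.303 = 0.641, 36% narrower.

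**Power, 48% versus 72%.** The facility-level variance is p(1−p)/150 + k²p², with noncentral t on the unmatched df:

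| CV | 2 vs 2, 2 df | 2 vs 2, 3 df | 4 vs 2, 4 df |
|---|---|---|---|
| 0.05 | 70% | 88% | 98% |
| 0.10 | 44% | 61% | 84% |
| 0.15 | 28% | 39% | 60% |
| 0.25 | 15% | 19% | 30% |

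At CV 0.25 the standard error falls from 0.158 to 0.128. That is more than 13%, because a constant CV gives the BFHI facilities the larger variance. With two matched sets (3 df), the pooled power at CV 0.25 is 26%.

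**The case against.** The strongest reply is that nothing here is in error. The planned contrast compares randomised arms, answers objective 1 and is unbiased; using one contrast for both objective 1 outcomes is coherent. That stands: the point is about efficiency.

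Several stronger readings are tempting, and the protocol does not support them.
- A reader might infer that a third of the facilities is wasted. The two facilities are unused for this outcome only; objective 2 depends on them.
- A reader might infer that most of the degrees of freedom are lost. It is half (2 of 4) against a two-arm analysis, and one of four against a three-arm model.
- A reader might take 44% as the value of the extra facilities. Most of it comes from t critical values in a facility-level test that the protocol does not plan. The protocol names GEE with a log-binomial model. With that model's usual normal-based intervals the gain is the 13% in the standard error, and whether such intervals are sound with so few clusters is a separate question.
- A reader might infer from the CV 0.10 row that pooling brings adequate power. That CV is not in the protocol.

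Pooling also carries an assumption. The protocol itself warns that its short-cut approach may not achieve full implementation, so delivery may differ between facilities. The planned questions on mothers' exposure to steps 3 to 9 can reveal a gross difference but cannot establish sameness with two facilities per arm. This calls for separate arm results as support. It does not bar pooling, since the intention-to-treat rule classifies by allocation whatever the uptake.

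The general wording about comparing intervention groups with controls leaves room for a combined comparison but does not override the specific sentence that names the BFHI steps 1-9 group.

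**Conclusion.** The point holds as a loss of efficiency in a valid contrast. For early initiation alone, the stated comparison leaves out two facilities that inform the same effect. Including them cuts the standard error by about 13% under equal facility variance. The t-based interval narrows by about 24% (three-arm, 3 df) or 44% (two-arm, 2 df) if facilities are analysed as unmatched; the matching described in the design section would change these df.

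The power gains rest on an assumed 72% rate and an assumed CV. At the only stated CV, 0.25 for EBF, power goes from 15-19% to about 30%. Pooling is worth doing but does not remedy having six facilities. The argument does not extend to EBF at 14 weeks or 6 months, because the arms differ by then.

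**What to change.** State, before any outcome data are seen, that the primary contrast for initiation within 1 hour is the four BFHI maternities (both intervention arms) against the two usual-care maternities. Use a small-sample cluster-level method whose df follow the allocation: 4 if unmatched, 3 with two matched sets of three. Say which applies. Report each intervention arm separately against usual care as supportive, alongside the exposure data on steps 3 to 9. Leave the EBF comparisons as planned.

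The cost is a sentence or two in the analysis section, with no new data, participants or procedures. The small downside is the assumption that steps 1-9 are delivered alike in both arms, which can be checked only roughly.

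### With two facilities per arm, the planned robust-variance GEE rests each contrast on four facilities and its nominal 95% interval covers about 70%; one pooled six-facility t analysis would be valid and use the third arm

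*Protocol*

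**What the plan says.** The Project Design and Implementation Plan states: "The selected six facilities will be randomized into 3 groups". The caption of Figure 2 gives "n = 150 per health facility, n = 300 per randomization group, and n = 900 total", so each arm has 300/150 = 2 facilities. The design section adds: "Facilities will be matched for these characteristics prior to randomization". It does not say what the matched sets are.

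The Evaluation section then sets one comparator per objective. For objective 1 (BFHI steps 1-9 against usual care), "the usual care group will provide the counterfactual". For objective 2 (well-child support added to BFHI steps 1-9), "the BFHI steps 1-9 group will serve as control and the proportion of infants with the outcome in the intervention group" is compared with that control.

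The modelling sentence reads: "Generalized Estimation Equation (GEE) and Log Binomial model will be used to estimate the prevalence ratio comparing interventions groups to controls". The section continues: "In GEE, the dependence within cluster is treated as nuisance". It claims valid inference provided that the mean structure is right, and attaches no condition on the number of clusters. It does not say how many models are fitted, and names no small-sample correction or t reference.

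**The concern.** With two facilities per arm, the scarce quantity is information on how much facilities differ from each other within an arm. A robust variance learns this only from the facilities in the two arms being compared, four in all, and treats the result as if it were known. The claim of valid inference relies on many clusters, which this trial does not have.

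The two facilities in the remaining arm also carry information on between-facility variation, and nothing in the plan uses it. At stake are intervals far too narrow for both primary contrasts, and then, once a valid method is adopted, avoidable imprecision if each contrast is analysed alone.

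**Working it through.** **Inputs.** All are from the Protocol's Evaluation section: coefficient of variation k = 0.25; 20% EBF under usual care and 40% under BFHI steps 1-9; minimum RR 1.5 (objective 1) and 1.3 (objective 2, from 45% upward); 150 per facility less 10% loss = 135; two-sided alpha 0.05.

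**1. The plan's own cluster figure.** Hayes-Bennett at 20% versus 40%, n = 150:

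c = 1 + (1.96 + 0.842)² × [0.16/150 + 0.24/150 + 0.25² × (0.04 + 0.16)] / 0.20² = 1 + 7.849 × 0.01517 / 0.04 = 3.98.

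The statement that the number falls below 4 reproduces. The formula counts clusters per arm, and the trial has 2.

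**2. One GEE or two.** With arm terms in the model, the robust standard error of a contrast depends only on the facilities in its two arms. Log-link GEE fits to simulated data gave the same standard error from the two-arm subset and from all six facilities (for example 0.1010 and 0.1010; 0.1145 and 0.1145). Adding the third arm to the planned GEE changes nothing.

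**3. Coverage of the z-based GEE interval.** Take an arm with two equal-sized facilities whose prevalences differ by d around mean p.

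- Robust variance of log p: 2(d/2)² / (2p)² = d²/(8p²).
- Unbiased variance, approximately: (d/p)²/2 divided by 2 = d²/(4p²).

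The robust variance is half the unbiased one, so the interval extends 1.96/√2 = 1.386 unbiased standard errors each side. On 2 df, P(|t| < x) = x/√(2 + x²) = 1.386/√3.921 = 0.70. Simulation (200,000 trials, lognormal facility prevalences with k = 0.25, 135 per facility, independence working correlation) gave 69-70% coverage and about 30% rejection under the null.

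**4. Valid facility-level alternatives on log prevalence.**

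- Two arms: df = 4 − 2 = 2, multiplier 4.303.
- Three arms pooled: df = 6 − 3 = 3, multiplier 3.182. The ratio is 0.740, or 0.769 in expected width when the variance is common.

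Simulated results with the same k in every arm:

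| Contrast | Mean half-width, 2 df | Mean half-width, 3 df | Change | Power, 2 df | Power, 3 df |
|---|---|---|---|---|---|
| Obj. 1, 20% v 40% | 1.11 | 0.83 | −25% | 28% | 41% |
| Obj. 1, 20% v 30% | 1.13 | 0.85 | −25% | 13% | 18% |
| Obj. 2, 40% v 52% | 1.02 | 0.83 | −19% | 9% | 10% |
| Obj. 2, 45% v 58.5% | 1.00 | 0.79 | −21% | 9% | 11% |

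Coverage was 95-96% for both t intervals and type I error about 5%. The GEE z half-width at 20% v 40% averaged 0.35.

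Analytic check at 20% v 40%: the variance per facility is 0.0625 + (1 − p)/(135p), that is 0.0921 and 0.0736. The standard error is √[(0.0921 + 0.0736)/2] = 0.288. Non-central t power is 28.4% on 2 df and 38.5% on 3 df.

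**5. If the matching formed two sets of three (an assumption).** A pairwise matched analysis has 1 df (multiplier 12.71). The joint analysis with set as a block has (2 − 1)(3 − 1) = 2 df (4.30).

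**6. Unequal facility variation.** With k = 0.35, 0.25 and 0.15 across the arms, pooling lowers objective 1 coverage to about 92%, and objective 2 gains little or nothing (from about 1% narrower to 5% wider, depending on how the simulation is set up).

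**The case against.** The strongest reply is that the quoted sentences only name comparators. A reader might infer that the plan fits separate four-facility models and discards the third arm, but the Protocol does not say so, and one three-arm GEE with two contrasts fits its wording equally well. That part of the objection stands.

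A reader might also infer that including the third arm would narrow the planned intervals by about a quarter at no cost. This is not supported either. Under the named GEE the gain is zero, the recommended intervals are wider than the GEE's, and pooling carries an assumption. Nor does the plan already make that assumption: its single coefficient of variation is an input to the cluster count for BFHI steps against usual care, not a condition of the analysis. The matched-set multipliers are conditional too, since no set structure is defined and no matched analysis is planned.

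It can further be said that small-sample corrections belong in a statistical analysis plan, which is not shown. That would excuse silence. Here, however, the Protocol claims validity for its method without regard to cluster number, and with four facilities per contrast the claim fails. If a correction exists elsewhere, the coverage shortfall may be met, and the remaining question is the pooling choice in step 4.

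**Conclusion.** The point holds in a limited form. Each planned contrast rests on four facilities under one model or two, and its z-based 95% interval covers about 70%. The z reference is the usual default for this method; the Protocol names no other. The algebra in step 3 shows that this shortfall comes from having two facilities per arm and hardly depends on the value of k.

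A pooled six-facility analysis on the log scale restores about 95% coverage. It gives intervals about 25% (objective 1) and 20% (objective 2) narrower than valid two-arm t intervals, with about 40% power instead of 28% at 20% versus 40%. These gains assume a common coefficient of variation in all arms and the log scale. Even then, power at the plan's minimum effects is only about 10-20%: two facilities per arm remain the binding limit.

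**What to change.** State in the Evaluation section that both contrasts, unchanged, come from one facility-level analysis of log prevalence in all six facilities, with arm as a three-level factor, one pooled between-facility variance and a t reference on 3 df. Define the matched sets. If they are two sets of three and the matching is kept in the analysis, add set as a block and use 2 df. Remove or qualify the statement that GEE inference is valid here.

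This needs no extra facility, mother or visit, but it replaces the inferential method rather than clarifying it. The costs are wider intervals than the GEE would report and the assumption of similar between-facility variation on the log scale in every arm. That assumption should be stated, because two facilities per arm cannot test it. Reporting the two-arm 2 df intervals alongside would show how far the conclusions depend on it.
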